## Abstract

**Background:**

Maternal, neonatal and child health outcomes are worse in families from black and ethnic minority groups and disadvantaged backgrounds. There is little evidence on whether lay support improves maternal and infant outcomes among women with complex social needs within a disadvantaged multi-ethnic population in the United Kingdom (UK).

**Method/Design:**

The aim of this study is to evaluate a lay Pregnancy Outreach Worker (POW) service for nulliparous women identified as having social risk within a maternity service that is systematically assessing social risks alongside the usual obstetric and medical risks. The study design is a randomised controlled trial (RCT) in nulliparous women assessed as having social risk comparing standard maternity care with the addition of referral to the POW support service.

The POWs work alongside community midwifery teams and offer individualised support to women to encourage engagement with services (health and social care) from randomisation (before 28 weeks gestation) until 6 weeks after birth.

The primary outcomes have been chosen on the basis that they are linked to maternal and infant health. The two primary outcomes are engagement with antenatal care, assessed by the number of antenatal visits; and maternal depression, assessed using the Edinburgh Postnatal Depression Scale at 8-12 weeks after birth. Secondary outcomes include maternal and neonatal morbidity and mortality, routine child health assessments, including immunisation uptake and breastfeeding at 6 weeks. Other psychological outcomes (self efficacy) and mother-to-infant bonding will also be collected using validated tools.

A sample size of 1316 will provide 90% power (at the 5% significance level) to detect increased engagement with antenatal services of 1.5 visits and a reduction of 1.5 in the average EPDS score for women with two or more social risk factors, with power in excess of this for women with any social risk factor. Analysis will be by intention to treat.

Qualitative research will explore the POWs' daily work in context. This will complement the findings of the RCT through a triangulation of quantitative and qualitative data on the process of the intervention, and identify other contextual factors that affect the implementation of the intervention.

**Discussion:**

The trial will provide high quality evidence as to whether or not lay support (POW) offered to women identified with social risk factors improves engagement with maternity services and reduces numbers of women with depression.

**MREC number:**

10/H1207/23

**Trial registration number:**

ISRCTN: ISRCTN35027323

## Background

Maternal, neonatal and child health outcomes are worse in women from black and ethnic minority and disadvantaged groups and there are a range of factors likely to be contributing, one of these being inclusivity and engagement with services. This was an important focus of the National Service Framework (NSF) [1] on Maternity and Maternity Matters [2], both of which emphasise choice, access and continuity of care in a safe service. The last two Confidential Enquiries into Maternal Deaths and Saving Mothers' Lives made recommendations about care for vulnerable women with socially complex lives [3]. Social disadvantage, living in a poor community and being from a minority ethnic group, including asylum seekers and newly arrived refugees, were all major risk factors. Black African women, including asylum seekers and newly arrived refugees had a mortality rate nearly six times higher than White women [3].^. ^Clearly maternal death is rare but it is well documented that women from these vulnerable groups book for antenatal care later, make fewer visits, experience greater pregnancy morbidity and have a higher risk of adverse fetal and child health outcomes. A recent UK national cohort study [4] found severe maternal morbidities were significantly more common among women from black African and Caribbean and Pakistani ethnic groups than in White women. The authors suggested that these differences may be due to pre-existing medical factors or factors related to care during pregnancy, labour or birth but they are unlikely to be due to differences in age, socioeconomic or smoking status, body mass index or parity. This study further highlighted the importance of tailored maternity services and improving access to care for women of ethnic minorities. Based on the assumption that increased engagement with antenatal services will result in improved maternal and perinatal health outcomes, the maternity NSF recommended that services are proactive in engaging all women, particularly those from disadvantaged groups. This includes contact early in their pregnancy and maintenance of contact before and after birth. It notes that some women in these groups may require more support and access to social or other services, for example housing and benefits advice.

In informing the NSF, evidence was sought on how services may be organised and delivered to improve outcomes for disadvantaged groups, but little good evidence was found [5]. The National Institute for Health and Clinical Excellence (NICE) has recently published a Guideline for Models of Service Provision for pregnant women with complex social factors [6] and found little high quality evidence. One of the research recommendations was to answer the question 'Is intervention and/or family support provided by statutory and 3^rd ^sector agencies effective in improving outcomes for women and their babies?'

Additional social support during pregnancy for vulnerable groups might, on the face of it, be of possible benefit. However, a recently updated Cochrane review of 'Support during pregnancy for women at increased risk of low birth weight' (LBW) [7] found 18 RCTs and concluded that programmes offering additional social support were not associated with improvements in any perinatal outcomes. In most of the trials, however, participants were selected because they had obstetric rather than social risks for LBW and almost all support interventions were delivered by trained professionals, which may not be the most likely person to improve outcomes. The review did find an overall reduction in Caesarean section (RR 0.87, 95%CI 0.78 to 0.97), and noted that some trials found improvements in maternal psychosocial outcomes [7]. It is well documented that a reduction in maternal depression, in addition to improving maternal wellbeing, will have a beneficial effect on short and long term child outcomes [8,9].

There is some evidence on benefits of lay support in other areas of maternity care from the Cochrane review on 'Continuous Support for Women during Childbirth' [10], which suggested that the beneficial effects associated with continuous support were greater when the provider was not a member of the hospital staff. The review showed that when the providers of continuous support were members of staff, spontaneous vaginal birth (SVB) was increased. When the providers of support were not staff members SVB appeared to be further increased. This therefore adds support to the hypothesis that care may be better received when provided by lay people rather than health professionals.

Evidence from three much quoted trials by Olds in the United States, of nurse home visitation from pregnancy up to 2 years for vulnerable groups (one mainly teen, single mothers [11] and the second, young deprived African-Americans [12]) found improvements in some pregnancy-related outcomes, including greater engagement with maternity and related services, and went on to find beneficial effects in several long-term maternal and child outcomes. Only the first trial, however, found any effect on preterm delivery and birth weight and only in the small sub-groups of those aged 14-16 and of smokers [11]. The third trial by Olds also examined the effects of home visitation by lay workers but found no benefit from this type of worker [13]. Evaluation of the Old's support model of nurse home visitation is currently being undertaken throughout the UK (Family Nurse Partnership (FNP)).

At present therefore, there is little evidence on whether lay support improves maternal and infant outcomes among women with complex social needs within a disadvantaged multi-ethnic population in the UK. A recent meta-synthesis [14] into barriers to antenatal care for marginalised women in high income countries has suggested that a non-judgemental, contextually tailored antenatal service that pays attention to the specific circumstances of disadvantaged women may increase sustained access to care.

So at least in theory, care that provides individual case management including home visiting, as provided by a POW service, could be of benefit.

The aim of this study is to evaluate, by a randomised controlled trial, a POW service for nulliparous women identified as having social risk within a maternity service that is systematically assessing social risks alongside the usual obstetric and medical risks.

## Methods/Design

### Design

The study design is an individually randomised controlled trial involving three primary care trusts (PCTs) in Birmingham, with nulliparous women assessed as having social risk, randomised to standard maternity care or the addition of referral to the POW support service (See Figure 1).

**Figure 1 F1:**
[figure not shown]
**Flow diagram to summarise allocation and contact throughout the trial**.

### Setting and population

The POW service and its evaluation will run across the whole of Birmingham, which currently comprises three PCTs: Heart of Birmingham (HoB PCT); South Birmingham (SB PCT) and Birmingham East and North (BEN PCT). Although varying in proportion, these PCTs all include a population that has high levels of deprivation and with a variety of ethnic groups, including many recently arrived mothers, refugees and asylum seekers. For example, in HoB PCT there are 5500-6000 births each year; almost 90% of which are to women in deprived wards (Index of Multiple Deprivation (IMD) quintile 5) [15]. Only about 15% are of European ethnicity, 54% are within the South Asian group (31% Pakistani, 11% Bangladeshi and 9% Indian), 13% are African and 10% African-Caribbean. One in four mothers has themselves been born outside the UK and many are recent immigrants who have little English language skills. In SB PCT, about 50% of births occur to women in the most deprived IMD quintile of deprivation and 60% of mothers are white. BEN PCT has a population somewhere between these in terms of the proportion of women in the ethnic minority groups and levels of deprivation. In summary, women from black and ethnic minority groups with complex social risk and needs accounts for a large and increasing proportion of the maternity population cared for by the three maternity units (Birmingham Women's National Health Service (NHS) Foundation Trust, Sandwell & West Birmingham NHS Trust, and Heart of England NHS Foundation Trust) in these PCTs.

### Usual care (control)

To maximise access and engagement with maternity services the local PCTs have commissioned a new service model based on social risk assessment, alongside assessing and managing obstetric and medical risk in the usual way. To assess social risk a set of items have recently been included in the standardised maternity notes used universally in Birmingham. These are completed at the booking visit by the midwife and identify whether a woman has any of the following factors:

• UK resident for under a year.

• Difficulty with the English language, both spoken and written.

• Housing problems, such as rent arrears, temporary accommodation, registered with National Asylum Support Service (NASS) or of No Fixed Abode (NFA).

• No support from either partner or family or friend

• Woman/household member in receipt of social services support, including child protection.

• Identified benefit problem.

• Smoking.

• Drug misuse, including other's in the household.

• Alcohol misuse.

• Clinical diagnosis of past or present mental illness.

• Teen parent (under 20 years old).

• Domestic abuse.

• Body Mass Index less than or equal to 18 OR more than or equal to 35.

• Late booking (defined as booking after 18 weeks gestation).

• Did Not Attend 2 or more antenatal appointments (under 28 weeks gestation).

The intention is that systematic social risk assessment will maximise the likelihood that social risk is identified and needs are met. Midwives identifying women with social risk factors currently either signpost women to services that may be beneficial or refer them to specialised agencies or personnel. This may mean they signpost to support agencies (for example, housing or benefit offices) or refer to other agencies (for example, social services), or refer onto the specialist midwives in their Trust. These specialist midwives act as a contact point and provide specific advice and support for women experiencing problems such as domestic abuse, mental health issues or who are teenagers when they are pregnant.

### Intervention

The PCTs have also decided to provide a POW service to complement these pathways, with the intention of further increasing full engagement with care during pregnancy and postpartum, and to improve the women's social conditions. The ultimate aim of this, theoretically at least, is to improve the health of both mother and baby by increasing engagement with antenatal services, which should reduce perinatal mortality and morbidity. It is also hoped that additional support of this nature would improve women's psychological health, which in turn would have a positive impact on the child.

The POW service is in addition to standard maternity care and will not be available to nulliparous women other than within the trial. Women assessed as having social risk and randomised to the intervention group will be referred to a POW who will provide individual case management including home visiting. The purpose of the POW service is to ensure that women attend antenatal appointments and engage with required care, such as taking prescribed medication, attending scan appointments, and including making lifestyle changes, such as smoking cessation. Additionally in the postnatal period the POWs are providing breast feeding support (World Health Organization Baby Friendly Initiative) and advice about feeding and caring for the baby. The POWs also provide social support on such issues as ensuring that available benefits are obtained, housing difficulties are dealt with, mental health problems managed and overall well-being is maximised. The philosophy underlying POW support is an attempt to help women to become more able to manage problems that arise in life, that is, to enhance their general self-efficacy. The POWs receive appropriate training to National Vocational Qualification (NVQ) level 3 which is provided by 'Gateway Family Services' and have access to supervision from experts with specific skills and knowledge. Postpartum POW contact will continue until 6 weeks after birth when transfer to the Family Support Worker (FSW) would take place for those who require it.

### Eligibility

#### Inclusion criteria

• Nulliparous women < 28 weeks gestation.

• Assessed by the midwife as having specified social risk through routine systematic assessment.

Nulliparous is defined as never having given birth to a child; this will include women who have had a miscarriage/s or termination/s of pregnancy. We have chosen under 28 weeks as an inclusion criterion to give adequate time for the POW service to impact on the outcomes.

#### Exclusion criteria

One of the PCTs (SB PCT) participating in this trial is also involved in a national trial of additional support to pregnant teenagers, called the Family Nurse Partnership (FNP). The FNP intervention is health professionals providing intensive support throughout pregnancy up to 2 years after birth. We will exclude teenagers recruited to FNP, but do not expect this to greatly affect recruitment to ELSIPS. We will also exclude those under 16 years of age due to the complexity of gaining informed consent from this group.

### Recruitment and randomisation

As part of the booking visit, all women in Birmingham have a systematic social risk assessment undertaken by the midwife. Once social risk has been identified the midwife will offer the support routinely available (as part of standard care) and will discuss the additional support of the POW only available through the trial. If the woman is potentially interested in taking part, her details will be passed to the ELSIPS midwife within the community midwifery team.

Randomisation is by random permuted blocked design stratified by Trust. The randomisation lists were generated by the trial statistician (KH) and then forwarded to the University of Birmingham Primary Care Clinical Research and Trials Unit who provided a telephone randomisation service thus ensuring concealment of allocation.

### The ELSIPS midwives

All the midwives within their individual teams refer eligible women to the ELSIPS midwife. The ELSIPS midwife is responsible for obtaining informed consent and randomising the women. They are also responsible within their teams for promoting the trial and training other midwives in trial processes. The ELSIPS midwives work for a varying number of hours (3-7) per week depending on the size of their team and the number of births. They each have an agreed target for the numbers of women we expect to be recruited each month. They are trained and supported by the University of Birmingham team.

### Outcome measures

The primary outcomes have been chosen on the basis that they are linked to maternal and infant health. The two primary outcomes are engagement with antenatal care, assessed based on number of antenatal visits, and maternal depression, assessed using the Edinburgh Postnatal Depression Scale [16] (EPDS) at 8-12 weeks after birth.

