### Sample size

Currently, NICE recommend, in the Antenatal Care Guideline [20], that the schedule of appointments should be determined by the function of the appointments and for nulliparous women with an uncomplicated pregnancy, they recommend that a schedule of ten visits should be adequate. The actual number of appointments attended was the subject of a survey of women's experiences of maternity care [21] carried out in 2006. This was a national survey which used a random sample of 4800 women and achieved a response rate of 63%. Women were sent a postal questionnaire three months after birth. Nulliparous women reported they attended a mean of 10.9 (standard deviation [SD] 6) antenatal appointments (Table 1).

**Table 1 T1:** Estimated frequency of the events which make up the primary outcomes

Outcome	Average	Source of information
Number of antenatal visits by nullips (consultant and midwife)	Average number of visits 10.9 (SD 6)	Recorded Delivery [21]

Edinburgh Postnatal Depression Scale (EPDS)	Average score5-7 (SD 6)	Psychosocial and psychological interventions for preventing postpartum depression (Cochrane review) [22]

There is some evidence relating to number of antenatal visits and perinatal outcomes. A systematic review [23] found that in settings where the number of visits is already low, reduced visits programmes of antenatal care for low risk women are associated with an increase in perinatal mortality compared to standard care, although admission to neonatal intensive care may be reduced.

An observational study explored the relationship between the number of antenatal visits made by 17,765 British women and adverse perinatal outcomes [24]. No consistent relationship between admission to neonatal unit or perinatal mortality and number of antenatal visits was found. A significant positive relationship was found between number of antenatal visits and Caesarean section, and low birth weight (less than 2500 g) was positively associated with number of visits for nulliparous women but not for parous women. More recently, a cohort study from Finland found under-attending free antenatal care was associated with adverse pregnancy outcomes [25]. Logistic regression analyses found there were significantly more low birthweight infants in the under and non-attenders, with more fetal and neonatal death.

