Estimates of the baseline Edinburgh postnatal depression score are taken from the controls of a Cochrane systematic review of Psychosocial and psychological interventions for preventing postpartum depression [22]. It is well documented that a reduction in maternal depression, in addition to improving maternal wellbeing, will have a beneficial effect on short and long term child outcomes and it is plausible that social support provided by the POWs could reduce the numbers of women becoming depressed. Studies have shown that depressed mothers are more likely to demonstrate impaired maternal-infant interactions and negative perceptions of infant behaviour [8]. Children of depressed mothers are more likely to suffer a range of adverse outcomes, including insecure attachment, behavioural problems, cognitive developmental deficits and difficulties in emotional functioning, some of these continuing into adolescence [9,26-29].

A sample size of 421 per arm would provide 90% power (at the 5% significance level) to detect a reduction of 1.5 in the average EPDS score from say 7 to 5.5, and would provide greater than 90% power to detect increased engagement with antenatal services of either 1.5 or 2 visits (Table 2). This calculation has also allowed for 20% drop-out or loss to follow-up.

**Table 2 T2:** Estimated sample size calculations for number of antenatal visits

Average number of antenatal visits	Average number in intervention arm	Difference	Power	Sample sizeper arm
8.9	10.9	2	90%	190

9.4	10.9	1.5	90%	337

Following a successful six month pilot in which 475 women were recruited a revision to the sample size was agreed. Prior to the pilot there was no data on the extent of the social risk factors amongst women and data from the pilot showed that 36% of the women recruited had one social risk factor. It was agreed to power the study to detect the pre-specified differences in the primary outcomes in the sub group of women with two or more social risk factors, which lead to an increase in the sample size to 658 women per arm. It is anticipated that this sample size of 1316 will be obtained by 31st December 2011.

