### Statistical analysis

We will calculate the mean number of visits and mean EPDS for each arm and compare differences using the *t*-test or other appropriate non-parametric test. Variations will be explored by pre-specified sub-group comparisons. Variations in participant baseline characteristics between intervention and control groups will also be explored, and if appropriate, variations in participant characteristics adjusted for using generalised linear models with appropriate consideration of strata of randomisation.

For secondary continuous outcomes, variations between control and intervention groups will be investigated using the *t*-test and, if necessary, covariate adjustment made using generalised linear models (to include strata affects); for secondary binary outcomes, differences will be compared using chi-squared tests and, if necessary, logistic regression. For all analyses, assumptions of various tests and models will be explored and non-parametric tests used if required.

All analyses will be by intention to treat and 95% confidence intervals will be quoted throughout. Missing covariate and outcome data will be examined. Reasons for withdrawal, lack of participation and any reasons for non-compliance will be documented and explored. Complete case and available case analyses will be completed in the first instance. If the amount of missing data is not insignificant, then multiple imputation will be used to evaluate sensitivity to the missing completely at random assumption, and inferences compared to those under the lesser missing at random assumption.

Pre-specified sub-group comparisons will be according to number of social risks (1 social risk or 2 or more social risks) identified and gestation at recruitment (< 12 weeks, 12-19 + 6 weeks, 20-27 + 6 weeks). These pre-specified subgroup comparisons will be for the primary outcomes and the more clinically important secondary outcomes (perinatal composite outcome, self-efficacy and Mother-to-infant bonding). The level of significance will at 0.05. The remaining secondary outcomes will have the level of significance at 0.01.

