## Discussion

The original intention of the ELSIPS trial was to include all pregnant women. However, our detailed investigations of current social support within the PCTs have found that many multiparous women with high social need will already have been allocated a FSW through their local Children's Centre. This is because multiparous women access the Children's Centres for services for their children under 5 years old and so come into contact with the FSW on a regular basis. These FSWs are provided through local education, as well as health services funding, and many provide very similar support to a POW. The main distinction between FSWs and POWs is the FSWs do not specifically engage with nulliparous women in the antenatal period. On this basis if multiparae were included, the trial comparison may fail to find a real difference because of the dilution effect of FSWs. In addition, contamination may arise if systematically more multiparae randomised to standard care who did not already have a FSW were subsequently provided with one because of not having been allocated to a POW.

We explored powering the study using a composite primary outcome of perinatal morbidity and mortality but the substantial sample size required to show even a large difference, together with funding constraints for the POW service whilst under evaluation, have meant we have opted for the smaller sample size required for the primary outcomes of engagement with services and EPDS at 8-12 weeks after birth. Although the scientific basis for antenatal care does not appear to be as robust as it might, it is based on the assumption that engagement with services results in improved maternal and perinatal health outcomes. So, the number of visits (both consultant and midwife) attended should act as a surrogate for improved maternal and neonatal outcomes.

We have chosen to evaluate self-efficacy as one of the psychological outcomes rather than self-esteem as it is more closely related to the changes the POWs are intended to facilitate. Self-esteem is believed to reflect evaluation of one's overall self-worth, while self-efficacy is specifically concerned with evaluation of one's performance [34]. We have chosen to evaluate differences in general self-efficacy rather than parenting specific efficacy because it is this broad construct that we believe will be promoted by the POWs.

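### Part of the antenatal visit count normally precedes randomisation, but the primary comparison does not routinely adjust for gestation at entry, so precision is forgone

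*Protocol article*

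**What the plan says.** - **Outcome.** Under Outcome measures, the outcome is "engagement with antenatal care, assessed based on number of antenatal visits". No start point is given. The Discussion makes clear that consultant and midwife visits both count: "the number of visits (both consultant and midwife) attended should act as a surrogate for improved maternal and neonatal outcomes".
- **Planning figures.** Sample size takes its mean and SD from a national postal survey done three months after birth: "Nulliparous women reported they attended a mean of 10.9 (standard deviation [SD] 6) antenatal appointments". Table 2 sets its target differences of 1.5 and 2 visits against that mean.
- **Entry and start of support.** The inclusion criterion is "Nulliparous women < 28 weeks gestation". Social risk is assessed at the booking visit (Recruitment and randomisation), and the Abstract has POW support starting at randomisation. Randomisation is stratified by Trust only.
- **Primary analysis.** Statistical analysis states "We will calculate the mean number of visits and mean EPDS for each arm" and compares the arms by a t-test or a non-parametric alternative. Baseline differences between arms are then explored, and generalised linear models are used for adjustment where that seems warranted. No covariate is named beyond consideration of the strata.
- **Role of gestation.** It appears in the analysis only as a subgroup factor: "gestation at recruitment (< 12 weeks, 12-19 + 6 weeks, 20-27 + 6 weeks".

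**The concern.** A woman's total is the sum of visits made before and after randomisation. Only the second part can respond to the POW. The first part varies between women, because entry spans a wide range of gestations and because late booking (after 18 weeks) and missing two or more appointments before 28 weeks are themselves qualifying risks. An unadjusted comparison leaves that variation in the error term.

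The plan's trigger for adjustment is also the wrong one. It depends on looking for differences between arms, but a covariate that predicts the outcome improves precision even when the arms are perfectly balanced. Choosing covariates after seeing the baseline table also leaves the primary analysis less than fully fixed in advance. At stake is a wider confidence interval than the data need give for a primary outcome, chiefly among women with two or more social risks, the group for which the trial was resized.

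**Working it through.** **Inputs from the article.** SD 6; difference 1.5 visits (9.4 against 10.9) or 2 visits (8.9 against 10.9); 5% significance, taken as two-sided because that reproduces the figures; 90% power; 20% loss; 36% of pilot women with one risk, so 64% with two or more; 658 per arm.

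**Step 1: reproduce the plan.** n per arm = 2 × SD² × (1.960 + 1.282)² / difference².

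- 1.5 visits: 2 × 36 × 10.507 / 2.25 = 336.2, so 337 (stated 337).
- 2 visits: 2 × 36 × 10.507 / 4 = 189.1, so 190 (stated 190).
- 20% loss: 337 / 0.8 = 421.25 (stated 421).
- Two-or-more-risk group: 421 / 0.64 = 657.8, so 658 (stated 658).

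Every figure reproduces with SD 6, the SD of a whole-pregnancy count. Variation in early visits is therefore already inside the sample size.

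**Step 2: power as planned.** Power = Φ(1.5 / (SD × √(2/n)) − 1.960).

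- Two or more risks: 658 × 0.64 × 0.8 = 336.9, so n = 337. The standard error is 6 × √(2/337) = 0.462, and Φ(3.245 − 1.960) = 90.1%.
- Whole trial: 658 × 0.8 = 526.4, so n = 526. The standard error is 0.370, and Φ(4.054 − 1.960) = 98.2%.

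**Step 3: bias.** Total = before + after. Under randomisation the expected count before randomisation is the same in both arms, so the expected difference in totals equals the expected difference in later visits.

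**Step 4: gain from adjustment.** Adjusted SD = 6 × √(1 − R²), where R² is the share of the variance in total visits explained by the baseline covariates. The article gives no value, so 0.05 to 0.25 is an assumption.

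| R² | Adjusted SD | Power, n = 337 | n per arm for 90% | 95% CI half-width, n = 337 | Power, n = 526 |
|---|---|---|---|---|---|
| 0 | 6.00 | 90.1% | 337 | 0.91 | 98.2% |
| 0.05 | 5.85 | 91.5% | 320 | 0.88 | 98.6% |
| 0.10 | 5.69 | 92.8% | 303 | 0.86 | 99.0% |
| 0.20 | 5.37 | 95.2% | 269 | 0.81 | 99.5% |
| 0.25 | 5.20 | 96.3% | 253 | 0.78 | 99.7% |

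The half-width is 1.96 × adjusted SD × √(2/337).

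**Step 5: would counting only later visits do better?** Assume early visits have SD s = 2 and correlation ρ with later visits, with the total SD held at 6. The later-visit SD is v = −ρs + √(36 − s²(1 − ρ²)). Adjusting the total for early visits has R² = ((s + ρv)/6)².

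| ρ | Later-visit SD | Power, later visits unadjusted | R² of adjustment | Power, total adjusted |
|---|---|---|---|---|
| 0 | 5.66 | 93.1% | 0.111 | 93.1% |
| −0.3 | 6.29 | 87.2% | 0.000 | 90.1% |
| −0.5 | 6.74 | 82.3% | 0.052 | 91.5% |

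A negative correlation is plausible, since a woman who enters late has less time for visits afterwards. Changing the outcome to later visits without adjustment could therefore lose power, whereas adjusting the total does not. Once the early count is a covariate, the arm coefficient is the same whether the response is the total or the later count, because the two differ only by that covariate.

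**The case against.** The strongest reply is that nothing is broken. The article does not say that visits before randomisation are counted, and a counting window is the kind of detail that a condensed article may leave to the full protocol. SD 6 belongs to the whole-pregnancy count, so the promise that 421 per arm "would provide greater than 90% power to detect increased engagement with antenatal services of either 1.5 or 2 visits" holds. Generalised linear models are already allowed. The total count fits the ten-visit schedule, the survey mean and the surrogate rationale. In the whole trial there is little power left to gain.

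Most of this stands. A reader might infer that the trial is underpowered, that the early visits bias the estimate, or that the outcome must be redefined. Steps 1 to 3 and 5 do not support any of these. Nor does the article show that late entrants have already made a large share of their visits: with late booking and missed appointments on the risk list, some may have made few. The absence of a counting window is not relied on here as a fault.

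What the reply does not answer is the choice of analysis. The article names the primary test, makes adjustment depend on observed differences, and gives gestation only a subgroup role. Those are stated choices, and a pre-specified adjusted model uses the same data better.

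**Conclusion.** The point holds as one of efficiency and pre-specification, not of validity. The planned sample sizes and the stated 90% power are sound, and the unadjusted estimate is unbiased. The cost is precision forgone: about 1 to 6 percentage points of power among women with two or more risks (90.1% to 91.5-96.3%), or a confidence interval roughly 3% to 13% narrower (1 − √0.95 to 1 − √0.75). In the whole trial power is already 98.2%, so there the benefit is mainly a narrower interval.

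This rests on two things that the article does not state outright: that the outcome is a whole-pregnancy count, inferred from the survey behind the planning mean, and that the covariates explain 5% to 25% of its variance. A lower R² would make the gain smaller. At trials of this size, adding so few covariates has no material cost in precision even if they explain almost nothing.

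**What to change.** Keep the total number of consultant and midwife visits as the outcome, and say that it covers the whole pregnancy if that is what is meant. Pre-specify the primary analysis as a linear model with arm, Trust (the randomisation stratum) and gestation at randomisation as a continuous covariate. Add the number of visits before randomisation where visits can be dated. Fit it regardless of observed imbalance, and use the same model within the two-or-more-risk group. The unadjusted difference in means can be reported alongside.

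The cost is a change of wording in the analysis plan. Gestation at recruitment is already needed for the subgroups and Trust for the randomisation, and the sample size does not change. The only extra work is splitting the visit count at the randomisation date. If only totals were extracted and visits cannot be dated, adjust for gestation and Trust alone.
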